### Study design

The study is designed as a cluster randomised controlled trial with GP practices as the unit of randomisation. To compare the whole intervention with both usual care and SSP only (to isolate the effect of the tool), the trial has three arms: the use of a monitoring and feedback tool embedded in the SSP (group 1), the SSP without the tool (group 2), and usual care (group 3). The CONSORT flowchart (Figure 
1) summarises the trial design. The population consists of 120 participants with COPD and 120 participants with DM2 from 24 GP practices. Each practice provides 5 COPD patients and 5 DM2 patients, which makes a total of 40 patients with COPD and 40 patients with DM2 from 8 practices per trial arm.

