##### Sample size and power calculation

For this study, 240 patients are required, with a minimum of 80 participants per group. Based on a validation study, we assume that the PA level of participants is an average of 24 minutes with a range of 14.6 minutes. A mean difference between group 1 and group 3 of ten minutes (42 %) of moderate to vigorous PA spent per day will be seen as clinically relevant. While assuming an intra-class correlation of 10 % based on practice, to account for the dependency of the data, with a power of 80 % and a significance level of 0.05, a total of 72 patients over 8 general practices are required in each group. Because a drop-out rate of 10 % is expected, practices will be asked to include 8–14 patients per practice in each subgroup, depending on the size of the practice.

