#### Data analysis for primary and secondary outcomes

An intention to treat analysis and a per protocol analysis will be conducted. For each outcome measure (all outcomes are continuous) data will be expressed as mean +/-SD. The between group comparisons will be analysed with multilevel analysis to account for the dependency of observations. We will apply a 3 level linear mixed model (time, participant, practice); the level of statistical significance will be set at 0.05 (two-tailed). Separate models (random intercept) will be set up for each outcome measure. The independent variables in each model are two dummy variables indicating the group, with the group of patients receiving usual care as the reference category and two dummy variables for time and their interaction effects. In addition, an extra dummy variable will be included to indicate the patient group (COPD versus DM2), to study whether the effects in COPD patients differ from the effects in patients with DM2. If needed, additional baseline variables will be included to account for possible confounding. If normality assumptions are violated, outcome variables will be log-transformed and if necessary non-parametric tests will be used. SPSS, version 19 and Mlwin, version 2.02 will be used to analyse the data.

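### The single COPD/DM2 dummy estimates a difference in activity level, not a difference in intervention effect, so the stated disease question goes unanswered

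*Protocol article*

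**What the plan says.** The Protocol article, section *Data analysis for primary and secondary outcomes*, sets out one three-level random-intercept model per outcome. The fixed part has two dummies for group, with usual care as reference, followed by "two dummy variables for time and their interaction effects". The next sentence adds disease: "an extra dummy variable will be included to indicate the patient group (COPD versus DM2), to study whether the effects in COPD patients differ" from those in DM2 patients.

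The article gives no product of the disease dummy with group or time, no model fitted separately by disease, and no other test of effect modification.

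The section *Study design* plans "40 patients with COPD and 40 patients with DM2 from 8 practices per trial arm", with five patients of each disease from every practice. Under *Health status*, the DSC-R is given only to DM2 participants and the CRQ-SAS only to COPD participants.

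**The concern.** The sentence gives the dummy a task that it cannot perform. In a model whose only interactions are group by time, the disease coefficient is one constant shift between COPD and DM2 patients, the same in every arm at every visit. The group-by-time terms, which carry the intervention effect, are common to both diseases. Equality of effects is thus built into the model instead of being examined.

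Two misreadings follow. If COPD patients are simply less active than DM2 patients, the dummy can be significant with no difference in effect. If the effects do differ, the difference is mixed with any difference in level and cannot be separated from it. A report that follows the text could then state that effects differ, or that they do not, from a coefficient that shows neither.

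**Working it through.** **1. Terms in the model.** Stated fixed part: intercept 1 + group 2 + time 2 + group-by-time 4 + disease 1 = 10 parameters. To let the effect differ by disease, add disease-by-group 2 + disease-by-time 2 + disease-by-group-by-time 4 = 8, giving 18.

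**2. What the dummy estimates.** Take balanced data (3 groups, 3 times, 2 diseases, equal cells). In the stated model:

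- dummy = (1/9) × sum over the nine group-time cells of (COPD mean − DM2 mean);
- group 1 by time = the intervention effect averaged over the two diseases.

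Let the intervention act in group 1 at t1 and t2, which is two of the nine cells. The scenario values are illustrative.

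| Effect in COPD / DM2 (min) | COPD − DM2 at baseline (min) | Group 1 by time | Dummy | Three-way term, full model |
|---|---|---|---|---|
| 10 / 10 | 0 | 10 | 0 | 0 |
| 20 / 0 | 0 | 10 | 2 × 20/9 = 4.44 | 20 |
| 10 / 10 | 4.44 | 10 | 4.44 | 0 |
| 20 / 0 | −4.44 | 10 | −4.44 + 4.44 = 0 | 20 |

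Rows 2 and 3 share the same group-by-time and disease coefficients, and so do rows 1 and 4. Only the intercept differs, and it reflects the overall activity level, not an effect. The 18-parameter model returns the true difference in effect in every row.

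**3. The plan's own sample size.** Inputs from *Sample size and power calculation*: the target is "A mean difference between group 1 and group 3 of ten minutes (42 %) of moderate to vigorous PA spent per day"; "with a power of 80 % and a significance level of 0.05"; ICC 0.10; 8 practices per arm; 10% drop-out. Activity is given as "an average of 24 minutes with a range of 14.6 minutes". I take 14.6 as an SD, which is an assumption.

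- Without clustering: 2 × [14.6 × (1.96 + 0.84)/10]² = 33.5, so 34 per arm.
- Design effect at 9 per practice: 1 + 8 × 0.10 = 1.8. With normal quantiles, 34 × 1.8 = 61.2, which does not give 72.
- With t quantiles on 2 × (8 − 1) = 14 degrees of freedom, the need is 69.7 per arm. The smallest whole cluster size reaching 80% power is 9, hence 72 per arm (power 81.3%; 8 per practice gives 78.9%).
- 72/0.90 = 80.

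The stated 72 and 80 are reproduced. They concern the overall comparison of group 1 with group 3.

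**4. Precision of the missing terms.** Use 72 analysable patients per arm, so 36 per disease, with disease balanced within practice. The contrast is the group 1 vs group 3 effect in COPD minus the same effect in DM2. It has four cell means.

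*Change from baseline*, which is what the three-way terms measure. The variance of one patient's change is 2(1 − ρ) × 14.6², where ρ is the within-person correlation; the practice intercept cancels. Then SE = 14.6 × √[8(1 − ρ)/36], and the detectable difference at 80% power is 2.80 × SE. The article gives no ρ, so a range is shown.

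| Assumed ρ | SE (min) | Detectable difference (min) | Power for a 10-min difference |
|---|---|---|---|
| 0.3 | 5.76 | 16.1 | 41% |
| 0.5 | 4.87 | 13.6 | 54% |
| 0.7 | 3.77 | 10.6 | 76% |

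*Single time point.* Both diseases share a practice, so the practice effect cancels and the factor (1 − 0.10) remains: variance = 4 × 14.6² × 0.90/36 = 21.3; SE = 4.62; detectable difference = 12.9 min; power for 10 min = 58%.

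**The case against.** The best defence is that the product terms were meant. The purpose clause states the right question, the disease sentence directly follows one on interactions, and an article condenses the full protocol. An analyst asked whether effects differ would probably fit the interaction. That may well describe the intention, but it does not repair the text. The section writes out interactions for group and time, introduces disease afterwards as one additional dummy, and ties the purpose to that dummy. This is a term given a role it cannot fill, not a detail left for later.

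Three stronger readings are tempting, and the documents do not support them.

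- *That disease is a core comparison, because equal numbers are recruited.* *Objectives and hypotheses* names the whole intervention against usual care, and then the isolated effect of the tool. The power calculation covers only group 1 against group 3. No hypothesis of different effects by disease is stated, and equal recruitment is not explained in that way.
- *That a real difference in effect would leave no trace.* In row 2 of the table it moves the dummy to 4.44. It is confounded with level, and it disappears only when a baseline gap happens to offset it, as in row 4.
- *That one detectable difference of about 13 min can be quoted.* The 12.9 min applies to a contrast at a single time point. The terms to be added measure change from baseline, where the figure depends on a correlation that the article does not give.

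**Conclusion.** The point holds for the secondary question of whether effects differ between COPD and DM2. As written, the model estimates a difference in level pooled over arms and times, and it constrains the effect to be common to both diseases. This follows from the structure of the model and needs no assumption about variance or sample size.

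Its reach is limited. With disease balanced within practices, as planned, the group-by-time terms still estimate the effect averaged over both diseases, so the primary comparison of group 1 with group 3 stands.

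Once the right terms are fitted, the estimate will be imprecise: the detectable difference in change is about 10.6 to 16.1 min for correlations of 0.7 down to 0.3, which is larger than the 10-min target for the overall effect throughout. These figures rest on reading 14.6 as an SD, 36 patients per disease per arm, and balance within practice.

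**What to change.** Amend the disease sentence in *Data analysis for primary and secondary outcomes*:

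- Keep the disease main effect and add disease by group, disease by time, and disease by group by time.
- Report the group 1 vs 3 and group 1 vs 2 effects for each disease, and the difference between diseases, with 95% CIs. Usual care is the reference, so group 1 vs 2 is a contrast of two coefficients.
- Label the analysis exploratory, and state that a non-significant interaction will not be read as equal effects.
- Omit the disease dummy from the DSC-R and CRQ-SAS models. Each covers one disease only, so the dummy is constant there. This is minor and does no harm once the dummy is dropped.
- If precision is stated, give a range with its assumptions, not one number.

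The cost is a short change of text and eight more fixed parameters, on data already due to be collected. The price is an imprecise exploratory estimate, which the confidence intervals will show.

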### Planned statistical analyses

#### Descriptive statistics

Demographic data (e.g., age, gender, disease, co-morbidities) will be described for the total group and for the subgroups separately. Continuous variables will be denoted with means, standard deviations, and medians. Categorical variables will be denoted in numbers and percentages. The participants included in the 3 arms will be tested on differences between characteristics, with chi-square, ANOVA (Kruskal Wallis).

If variables differ between groups, with a p-value ≤0.10, they will be considered to be potential confounders in further analysis.

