## Discussion

This study fills a gap in the literature about how to improve self-management of patients with COPD or DM2 in increasing their level of PA by using technology embedded in primary care.

Post-recruitment selection bias, a well-known problem of cluster randomised controlled trials, will be partly avoided by asking the nurses to include patients and send a general invitation letter before the randomisation of the practices. But not informing the patients about the intended intervention (the randomisation outcome of their GP practice), is insuperable because patients have to be informed about the intervention before they agree to participate.

During a pragmatic trial, which aims to measure the effectiveness of an intervention in routine practice, it is important to collect process data to avoid Type III errors (evaluating an intervention that was inadequately implemented). In choosing the outcomes and measurements of the process evaluation, the potential for increased Hawthorne effects will be taken into account by minimising the contacts between researchers and participants, and by avoiding overlapping roles between researchers and PNs, for example by asking the PNs to include patients for the study, and by arranging an independent helpdesk. Patients will not be interviewed during the intervention in order to distinguish between the intervention and its evaluation.

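### Baseline variables added as main effects adjust the t0 difference between arms, but leave the group-by-time effect essentially unadjusted for confounding of change

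*Protocol article*

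**What the plan says.** In the protocol article, the section on data analysis for primary and secondary outcomes sets out a three-level linear mixed model (time within participant within practice) with random intercepts. Its fixed effects are two group dummies with usual care as reference, "two dummy variables for time and their interaction effects", and a dummy for disease. It then adds: "If needed, additional baseline variables will be included to account for possible confounding".

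The candidates for adjustment come from the section on descriptive statistics. Variables that differ between arms at p ≤ 0.10 are flagged, and "they will be considered to be potential confounders in further analysis".

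The recruitment section has nurses identify and write to eligible patients before randomisation. Patients are then telephoned after randomisation, told what their practice's group involves, and asked whether they will take part. The Discussion acknowledges the consequence: "Post-recruitment selection bias, a well-known problem of cluster randomised controlled trials, will be partly avoided".

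The sample size section expects 10 % dropout, and the section on missing data says follow-up values will not be imputed.

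**The concern.** The stated purpose of the extra variables is to deal with confounding. The coefficient that carries the intervention effect is a difference in change, and a term that is constant over a participant's visits cannot act on a change. On the natural reading the adjustment therefore works on the t0 difference between arms, where no treatment effect is sought, and hardly touches the contrast of interest.

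Two things are at stake. First, if patients who accept the tool differ from those who accept usual care in something that predicts how activity evolves, that bias stays in the result labelled as adjusted. Second, adjusted and unadjusted estimates will nearly coincide because of the model's structure, and a reader may take that as reassurance. The second risk does not depend on any assumed effect size. The point concerns how variables enter the model, so it holds equally for a well-chosen prespecified set.

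**Working it through.** **1. Which coefficient is the effect.** There are three measurement times and two time dummies, so t0 is one of the outcomes. With group-by-time terms, the between-arm effect at t1 and t2 is the interaction. This fits the main hypothesis, which is about an increase that is then maintained.

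**2. What a main effect does.** Write participant i in practice c at time t as

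Y = β0 + β_g + τ_t + γ_gt + δx + u_c + v_i + e_t.

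Then Y_t − Y_0 = τ_t + γ_gt + (e_t − e_0). The terms δx, u_c and v_i all cancel. If every participant has all three visits, γ is estimated only from these within-participant changes, so adding x leaves the estimate of γ identical. This does not depend on the variance components.

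**3. What is left uncontrolled.** If x also predicts change, with slope φ, and the arms differ by Δ in mean x, then E(estimate of γ) = γ + φΔ. If x affects level only, φ = 0 and there is no bias even without x in the model.

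**4. The plan's own figures, for calibration.** The sample size section gives "A mean difference between group 1 and group 3 of ten minutes (42 %) of moderate to vigorous PA spent per day" and "the PA level of participants is an average of 24 minutes with a range of 14.6 minutes". I read 14.6 as a standard deviation, which is an assumption.
- Per arm without clustering: 2 × (14.6 × 2.80 / 10)² = 33.5.
- Design effect with 9 per practice and ICC 0.10: 1 + 8 × 0.10 = 1.8, giving 60.2.
- With t quantiles on 14 df (8 + 8 practices): 69.7 per arm, or 8.7 per practice. Rounded up to 9, that is 72, and 72 / 0.9 = 80.

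The stated 72 and 80 reproduce. They do not bear on the point, but they support the inputs used below.

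**5. Simulation.** From the plan: 24 practices of 10 patients, three visits, ICC 0.10, SD 14.6, true effect 10 min. Assumed: the remaining variance split into 50 % participant and 40 % residual (of the total); x imbalanced by Δ = 0.5 SD in group 1; level effect 6 min per SD; φ = 0 or 4 min per SD; covariate-dependent dropout with logit −2.5 + x. There were 400 trials per row, with known variances. The table gives the mean group 1 versus group 3 estimate at t1.

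| Scenario | No x | x main effect | x and x-by-time | Mean shift from main effect | Largest single-trial shift |
|---|---|---|---|---|---|
| Complete, φ = 0 | 10.07 | 10.07 | 10.07 | 0.00 | 0.00 |
| Complete, φ = 4 | 12.07 | 12.07 | 10.04 | 0.00 | 0.00 |
| 10 % random dropout, φ = 0 | 10.11 | 10.11 | 10.10 | 0.00 | 0.49 |
| 10 % random dropout, φ = 4 | 11.92 | 11.92 | 9.92 | 0.00 | 0.58 |
| Dropout depends on x, φ = 0 | 9.79 | 9.89 | 9.84 | 0.10 | 0.95 |
| Dropout depends on x, φ = 4 | 11.67 | 11.83 | 9.92 | 0.16 | 0.99 |

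The Monte Carlo error of a mean is about 2.2 / √400 = 0.11 min. The excess of about 2 min where φ = 4 with complete data matches φΔ = 4 × 0.5 = 2.0.

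A single REML fit to one complete dataset shows the invariance directly. The interaction was 9.504877 with and without x, and 7.174356 with x-by-time added. The t0 group difference moved from 2.60 to −1.51 when x entered as a main effect.

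**6. Range of bias.** For Δ of 0.3 to 0.5 SD and φ of 1.5 to 4 min per SD, the bias runs from 0.3 × 1.5 = 0.45 min to 0.5 × 4 = 2.0 min. For scale, with 80 per arm and clustering ignored, a two-arm comparison reaches p = 0.10 at a gap of 1.645 × √(2/80) = 0.26 SD. Imbalances near 0.3 SD are therefore the kind the plan's own flag picks up. The document gives no value for φ.

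**The case against.** Several stronger statements are tempting, and the document does not support them.

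- **That the adjustment can never change the primary estimate.** This is exact only with complete follow-up. The plan expects 10 % dropout without imputation, and a real trial is one dataset, in which shifts of about 0.6 to 1 min are possible. A main-effect covariate related to dropout also has a legitimate role under missing at random. None of this removed the confounding of change in the simulations.
- **That confounding is not accounted for at all.** The interaction already removes stable differences in level: 10.07 against a truth of 10 with no covariate. Only variables that are both imbalanced and predictive of change remain.
- **That the plan rules out covariate-by-time terms.** It neither states nor excludes them. The disease dummy is also described merely as included, although its stated aim of comparing effects between diseases needs interactions. An article may also leave model detail to a fuller plan. Against this, the article does spell out the group and time interactions and gives none for confounders, so main effects only is the natural reading.
- **That the result is known to be materially biased.** The imbalance and slope are assumed. The design also gives some protection, through identification before randomisation and stratification by practice size, and no covariate can cure selection on unmeasured factors.

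A claim of lost precision would also be weak. In one fitted example the standard error was 1.918 without and 1.908 with covariate-by-time terms, a gain of about 0.5 %.

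**Conclusion.** The point holds in a limited form. On its natural reading, the planned adjustment corrects the t0 difference between arms and leaves the group-by-time effect exactly unchanged with complete data, and nearly unchanged on average with the expected dropout. It does not control confounding of change, which is plausible here because consent follows knowledge of allocation. Close agreement between adjusted and unadjusted results would say little about whether such confounding exists.

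The invariance follows from the model alone. The size of any bias does not: about 0.5 to 2 min of the 10-minute effect rests on assumed imbalances of 0.3 to 0.5 SD and slopes of 1.5 to 4 min per SD. The core model is otherwise sound for a randomised comparison. This is a worthwhile and cheap improvement, not a must-fix.

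**What to change.** In the section on data analysis for primary and secondary outcomes, state that each adjustment variable enters with its main effect and its interactions with both time dummies.

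The alternative is to model t1 and t2 only, with the t0 value and the adjustment variables as covariates; main effects then act on the group contrast. The two are not equivalent. When t0 is imbalanced, they differ by roughly (1 − ρ) times the t0 gap. With an assumed within-person correlation of 0.7 and a gap of 0.3 SD (0.3 × 14.6 = 4.4 min), that is 0.3 × 4.4 = 1.3 min. One of them should therefore be chosen in advance.

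Report the group 1 versus group 3 estimate with and without adjustment.

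The cost is one sentence, two extra coefficients per covariate under the first option, and a few degrees of freedom. No new data are needed.

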#### Data analysis process evaluation

Quantitative data will be analysed by means of descriptive statistics. In order to identify relevant themes, qualitative data (results of open-ended interviews and focus groups) will be independently analysed by two researchers using NViVo version 9. A concurrent triangulation strategy will be applied to confirm, cross validate and corroborate the findings.

### Procedure for accounting for missing, unused and unexpected data

Accounting for missing values on items in questionnaires will be handled according to the scoring algorithms of the questionnaires. Missing variables in follow-up data will not be imputed since it has been shown that multilevel analysis is a very flexible method for handling missing data
[45].

### Stopping rules

There are no formal statistical stopping rules. If a patient decides to withdraw (e.g., hospital admission), the nurse may discontinue the intervention, but all participants will be asked to complete follow-up assessments. Patients can withdraw from the study at any time.

### Ethical principles

The study protocol was approved by the research ethics committee of azM/UM, Maastricht, the Netherlands in 2013 (METC12-3-071).

## Discussion

This study fills a gap in the literature about how to improve self-management of patients with COPD or DM2 in increasing their level of PA by using technology embedded in primary care.

Post-recruitment selection bias, a well-known problem of cluster randomised controlled trials, will be partly avoided by asking the nurses to include patients and send a general invitation letter before the randomisation of the practices. But not informing the patients about the intended intervention (the randomisation outcome of their GP practice), is insuperable because patients have to be informed about the intervention before they agree to participate.

During a pragmatic trial, which aims to measure the effectiveness of an intervention in routine practice, it is important to collect process data to avoid Type III errors (evaluating an intervention that was inadequately implemented). In choosing the outcomes and measurements of the process evaluation, the potential for increased Hawthorne effects will be taken into account by minimising the contacts between researchers and participants, and by avoiding overlapping roles between researchers and PNs, for example by asking the PNs to include patients for the study, and by arranging an independent helpdesk. Patients will not be interviewed during the intervention in order to distinguish between the intervention and its evaluation.

